#### OurGILL

The OurGILL module focuses on systematic (i.e. in design, frequency, and imbedding in daily care) and comprehensive somatic screening, and promotes the prevention, early recognition, and treatment of physical problems. It aims to assess clients’ psychiatric condition, physical symptoms and complaints, medication use and side effects, specific measurements (e.g. BMI, waist circumference, laboratory measurements), and observations (e.g. extrapyramidal movement disorders). OurGILL provides an overview of physical abnormalities, which forms the basis for a personalised somatic treatment plan.

#### MyGILL

The MyGILL module is aimed at lifestyle behaviours, including nutrition, physical activity, sleep, relaxation, substance use and addiction, personal hygiene, smoking, sex life, and social support. The result is an overview of the client’s performance in these lifestyle areas. This facilitates drawing up a personalised lifestyle plan based on the client’s preferences and capabilities. The client will be guided towards the SMART formulation of lifestyle goals (specific, measurable, acceptable, realistic, and time-bound). The MyGILL module is available on both the internet platform and a mobile device application.

The two modules, OurGILL and MyGILL, are complementary and can be executed simultaneously. Implementing the two modules costs at least two hours, depending on the client’s technical abilities and self-management skills. The coordinating nurse (mental health nurse or nurse practitioner) will have a central position as ‘care manager’ when implementing the eHealth intervention, to ensure effective coordination and continuity of care within the multidisciplinary treatment context.

### Usual care

The teams assigned to the control group will not receive any training and will provide care as usual. Clients in the usual care group will have unrestricted access to mental and general health care, but are not allowed to participate in a structured lifestyle programme for the duration of the study. National guidelines are used as frame of reference for usual care, but the implementation of usual care is currently variable between teams and mental healthcare facilities. To obtain a clear overview of the care as usual as currently delivered, a questionnaire will be filled out at baseline for all participating teams focusing on the execution of somatic screening and lifestyle interventions.

### Training of care managers

The GILL eHealth intervention will be conducted by trained coordinating nurses, who will perform the role of ‘care manager’ for physical health and lifestyle. Two nurses of each team in the experimental condition will receive a one-day training focused on the theoretical background of physical health care and lifestyle promotion for clients with SMI. Most of the training time is spent on practical skills for the effective provision of the screening and lifestyle intervention to the client. Special attention is paid to motivational skills, promoting clients’ commitment to the intervention, and realising their optimal use of self-management skills. Since these nurses will act as care managers, they will be trained in how to involve the client’s social network and how they can assist in supporting clients to improve their physical health. Two eLearning modules need to be completed before participating in the training.

During the one-year follow-up period feedback sessions will be organised every three months for the nurses in the experimental condition. These sessions will be supervised by the expert trainer, focusing on barriers and successes during the implementation of the intervention. The sessions aim at learning from each other. This also provides the opportunity to detect possible bottlenecks during the implementation process, for example related to personal or organisational factors that hinder execution of the intervention. The training will be given by an experienced trainer in physical health and lifestyle promotion in mental health care. The trained nurses can function as role models within their team and disseminate their gained knowledge to other team members. Besides the structured training and feedback meetings, nurses can always contact the training staff to discuss any questions or problems that may arise.

### Main study outcomes

#### Primary outcome

Primary outcome of this study is metabolic syndrome severity, and is operationalised by the Metabolic Syndrome Severity Score (MSSS) at 12 months as defined by Gurka et al. [26]. This is the primary outcome given that the included clients have overweight/obesity (BMI 27 and higher) and a significantly increased risk of metabolic abnormalities. MSSS includes the components gender, ethnicity, systolic blood pressure, waistline circumference (cm), high-density lipoprotein, triglycerides, and fasting blood glucose [26–28].

#### Secondary outcomes

Secondary clinical outcomes are weight (kg), BMI (kg/m2), diastolic blood pressure, lipid profiles (LDL, total cholesterol), and HbA1c. Participants will also perform a six-minute walk test (6MWT) to assess physical fitness [29]. The 6MWT is a reliable and valid measure of cardiovascular fitness for overweight/obese adults [30, 31] and has been previously used in clients with SMI [32].

#### Client reports

Several client reports will be used in this study. The International Physical Activity Questionnaire Short Form (IPAQ-SF) [33] will be administered to measure each participant’s general level of physical activity. IPAQ-SF is a self-report questionnaire where participants recall the number of days and minutes of vigorous activity, moderate activity, walking time, and sitting time over the past 7 days. IPAQ-SF has been used extensively in other psychiatric populations and has acceptable validity and reliability [34, 35].

Perceived satisfaction with physical health, physical activity, and healthy eating will be measured using a numeric rating scale (NRS), with a score ranging from 0 to 10. The self-assessment concerns the past four weeks and has proven feasible [36].

Quality of life is measured using the 12-item Short-Form survey (SF-12). This is a generic, reliable and validated instrument containing 12 items derived from the 36-item Short-Form survey (SF-36) [37]. Physical and mental quality of life will be measured using the physical and mental component summary of the SF-12.

Recovery is assessed with the Questionnaire about Processes of Recovery (QPR) [38]. The QPR is a self-report 15-item questionnaire with a score range of 0–60 (QPR total) with good internal consistency and test–retest reliability properties [39]. In this study the QPR total, intrapersonal, and interpersonal scores for participants will be calculated.

Health-related self-efficacy is measured by the Patient Activation Measure (PAM-13), a reliable questionnaire containing 13 items derived from the original PAM-22 [40]. The questionnaire assesses participants’ self-reported knowledge, skills, and confidence for health-related self-efficacy. Personal views on physical and mental health, nutritional status, physical activity status, and sleep will be asked by giving a score from fully disagree to fully agree.

#### Clinician-rated

Psychosocial functioning will be measured with the Health of the Nation Outcome Scale (HoNOS) [41]. The HoNOS is an instrument comprising 12 items on four domains (behavioural problems, organic problems, psychological symptoms, social problems), each item ranging from 0 (no problems) to 4 (severe problems). Total psychosocial functioning will be indicated by the sum of all items. The scale shows good psychometric properties [41] and is used in the large majority of lifestyle programmes among severe mentally ill residential clients [42].

#### Demographics

Demographic and clinical data (i.e., age, gender, ethnicity, marital status, educational level, employment status, psychiatric diagnoses, diagnoses of physical diseases, current smoking status) will be obtained at baseline to describe our sample, to control for possible confounders, to determine the MSSS, and to analyse the effects of sociodemographic situations on the results of the intervention.

#### Utilisation of health care

Utilisation of the medical health care will be measured by the Treatment Inventory of Costs in Clients with psychiatric disorders (TIC-P) [43]. TIC-P is a validated questionnaire designed for self-report in adult clients with a mental disorder. It is a generic questionnaire, which means that the items are not related to one specific disease in mental health. The TIC-P items to be used include 20 structured questions on the volume of medical costs, e.g., ambulatory services, private practice, and general practitioner.

For an overview of the outcome measurements, instruments, and data collection schedule during the GILL study period, see Table 1.

**Table 1 Tab1:** Outcome measurements, instruments, and data collection schedule of the GILL e-health intervention

	**Baseline**	**6**	**12**
**SOMATIC HEALTH**			
Metabolic syndrome severity^a^	x	x	x
Waistline circumference (cm)	x	x	x
Blood pressure (mm/hg)	x	x	x
Lipid profiles^b^	x	x	x
Fasting blood glucose (mmol/l)	x	x	x
BMI (kg/m^2^)	x	x	x
Physical fitness (6-min walking test)	x		x
**CLIENT REPORTS**			
Physical activity (IPAQ-SF)	x	x	x
Perceived lifestyle behaviours (NRS)	x	x	x
Quality of life (SF12)	x	x	x
Recovery (QPR)	x	x	x
Health-related self-efficacy (PAM-13)	x	x	x
**CLINICIAN-RATED**			
Psychosocial functioning (HoNOS)	x	x	x
**DEMOGRAPHICS**^c^			
Age, gender, ethnicity	x		
Marital status	x		
Educational level	x		
Employment status	x		
Current psychiatric diagnoses	x		
Diagnoses of somatic diseases	x		x
Current smoking status	x	x	x
Number of years receiving mental care	x		
**COSTS**			
Healthcare utilisation (TIC-P)^d^	x	x	x
Medication use	x		x
**OTHER**			
Compliance with group sessions		Weekly /monthly	
Adverse event reporting		Ongoing collection	

^a^Also employs the components sex, age, and ethnicity

^b^Cholesterol: high-density-lipoprotein, low-density-lipoprotein, total and triglycerides (mmol/L)

^c^Based on client medical records

^d^TIC-P, measured at baseline and at 3, 6, 9 and 12 months

#### Process evaluation

This study also includes a qualitative process evaluation at the client and nurse level. Barriers and facilitators for effective use and implementation of GILL eHealth will be investigated. At the client level the goal is to understand participants’ experiences and perceptions with GILL eHealth, their responses to the different elements of the intervention, and their appreciation of the nurses’ support and coaching. At the nurse level the goal is to examine their experiences and perceptions with GILL eHealth and understand its feasibility and acceptability.

To organise the semi-structured interviews, a topic guide will be developed based on study aims, the content and procedures of the GILL eHealth intervention, clients’ and nurses’ feedback during the rollout of the intervention, and the observations during the feedback meetings. The interviews will be conducted with 15 clients and 15 trained nurses. Other input for the process evaluation will come from an implementation group formed at the start of the project, to enhance the implementation and dissemination of the intervention. The group will consist of representatives of clients and family members, nurses, educators/teachers, and managers. They will provide input in at least three formal meetings on multiple aspects of implementation, such as the content of training and implementation strategies during the study.

The results of the process evaluation will be translated into recommendations for the implementation guide, developed during the final stage of the project. The implementation guide will be developed using the framework of Fleuren et al. [44] and will include an evidence-based multifaceted strategy that matches the facilitators and barriers identified in the process evaluation.

#### Sample size

This RCT is powered to detect a mean difference of at least 0.40 in the metabolic syndrome severity Z score across 1 year between the intervention and control group. The mean difference in the metabolic syndrome severity Z score is estimated on the basis of earlier intervention studies [27, 45]. With a power set at 0.80, and an alpha of 0.05, two groups of 98 patients with SMI are needed in each group. Assuming an inclusion of 10 clusters (teams) within each arm, and assuming an ICC of 0.01 implies that 220 patients are required. Assuming a dropout rate of 15% [46, 47] and testing the intervention effect using two samples t-test, implies that we need to recruit a total of 258 patients. However, testing of the intervention effect by use of linear mixed models is likely to reduce bias and increase power [48].

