### Statistical analysis

Baseline data will be presented comparing the two treatment groups. Both intention-to-treat and per-protocol analysis will be conducted. To test the hypothesis that the tailored eHealth intervention will result in improved metabolic syndrome severity in SMI clients compared to usual care, linear mixed models will be used. The obtained betas describe the reduction in metabolic syndrome (Mets) Z score in the intervention group relative to the control group. Mixed-model analyses take the dependence of the repeated measurements into account, while using the maximum amount of information that is present in the data [49]. The main analyses will consist of fully corrected models. These models will be corrected for baseline values of the respective outcome plus include the covariates gender, age, and any other possible confounding variables on which the treatment groups differed at baseline. Also, ANCOVA will be used with the change of the Mets Z score (baseline – 12 months) as the outcome variable. Explanatory variables are gender, Mets Z score at baseline, and study group (intervention vs. control). The eHealth intervention succeeds if the lower mark of the two-sided 95% confidence interval is larger than zero. To test for within-group differences from baseline to the end of the intervention period, a repeated-measures ANOVA will be applied. The type-1 error is set to 5% (two-sided). For secondary outcomes, linear and logistic mixed models (depending on the outcome) will also be used to test the differences between the two groups. Missing values after 12 months will be conservatively replaced by the baseline-observation-carried-forward method to avoid an overestimation of the effect through dropouts.

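### The clustering allowance omits the small-sample correction for 20 randomised teams: a valid unadjusted t-test has about 0.76 power, not 0.80

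*Protocol article*

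**What the plan says.** The Sample size section describes the trial as "powered to detect a mean difference of at least 0.40 in the metabolic syndrome severity Z score across 1 year". The calculation has three steps:

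- Before clustering: "With a power set at 0.80, and an alpha of 0.05, two groups of 98 patients with SMI are needed in each group".
- Clustering: "Assuming an inclusion of 10 clusters (teams) within each arm, and assuming an ICC of 0.01 implies that 220 patients are required".
- Dropout of 15%, and the test assumed: "testing the intervention effect using two samples t-test, implies that we need to recruit a total of 258 patients".

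The section closes with a general remark that linear mixed models would probably lessen bias and raise power; no figure is attached. Neither an SD nor a baseline-to-follow-up correlation is given.

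The Statistical analysis section makes a linear mixed model, corrected for the baseline value of the outcome, the main analysis, and adds: "The type-1 error is set to 5% (two-sided)". The Randomisation section allocates whole teams. The Setting section expects about 20 facilities and allows teams to be added if enrolment lags.

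**The concern.** In a cluster-randomised trial the team is the unit of randomisation, so the precision of the treatment comparison has to be judged against variation between teams. A design effect enlarges the variance for clustering. It does not change the reference distribution, which with few teams has noticeably heavier tails than the normal. With 10 teams per arm, an unadjusted comparison has 2 × 10 − 2 = 18 degrees of freedom and a two-sided 5% critical value of 2.101, against 1.96 for the normal approximation. If the calculation uses the latter, the stated power is too high for the test that it names.

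At stake is how a null result would be read. Readers will judge it against a stated 0.80. If the named test does not have that power, the figure needs another basis or a lower value.

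**Working it through.** **Inputs.** From Sample size: difference 0.40, power 0.80, alpha 0.05, 10 teams per arm, ICC 0.01, 220 evaluable (110 per arm, 11 per team), 15% dropout, two-sample t-test. From Statistical analysis: two-sided testing. Assumed: SD = 1. The article does not state it, but the outcome is a Z score and SD 1 is the value that returns 98 per group.

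**Reproducing the plan's figures.**

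- Unclustered: n = 2 × (1.960 + 0.842)² / 0.40² = 98.1 per group (stated 98).
- Design effect at 11 per team: DE = 1 + (11 − 1) × 0.01 = 1.10. Then 98 × 1.10 = 107.8 per arm, about 216 in total; rounding up to 11 per team gives 20 × 11 = 220 (stated 220).
- Dropout: 220 / 0.85 = 258.8 (stated 258).
- Power at 220: effective size 110 / 1.10 = 100 per arm, giving 0.807 by the normal approximation, or 0.804 from the noncentral t with 218 degrees of freedom.

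So the stated 0.80 follows from the large-sample method.

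**The same inputs with 18 degrees of freedom.**

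- Noncentrality: 0.40 / √(2 × 1.10 / 110) = 0.40 / 0.1414 = 2.83.
- Noncentral t, 18 degrees of freedom, critical value 2.101: power 0.763. With 219 evaluable (258 less 15%) it is 0.761.
- Difference detectable with 0.80 power: noncentrality 2.963, and 2.963 × 0.1414 = 0.419.

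**Simulation (40,000 trials, 11 per team, ICC 0.01).**

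| Test | Power | Type I error |
|---|---|---|
| t-test on team means | 0.762 | 0.049 |
| Client-level t-test ignoring teams | 0.830 | 0.061 |

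The client-level test exceeds 0.80 only by not holding the 5% level.

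**Effect of baseline adjustment.** With baseline-to-12-month correlation ρ and the ICC held at 0.01, the residual SD is √(1 − ρ²). Power of 0.80 with 18 degrees of freedom requires 1 − ρ² = (0.40 / 0.419)² = 0.911, so ρ ≈ 0.30. The values of ρ below are assumptions.

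| ρ | 0 | 0.3 | 0.5 | 0.7 |
|---|---|---|---|---|
| Power (18 df) | 0.76 | 0.80 | 0.87 | 0.96 |

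**What 0.80 would take without adjustment.** About 246 evaluable in 20 teams (12.3 per team; 246 / 0.85 ≈ 290 recruited), or 11 teams per arm with 11 evaluable each (242 evaluable, power 0.806).

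**The case against.** The strongest reply is that the t-test serves only to size the trial. The main analysis is a baseline-adjusted mixed model, the article says that this is likely to raise power, and a modest correlation is enough to recover 0.80 even with 18 degrees of freedom. This stands. A reader might infer that the primary analysis is underpowered; the documents do not support that, because the deciding correlation is not given. Equally, the article does not show that power is adequate, since it leaves the gain unquantified.

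A second reply is that nothing is miscalculated: design-effect inflation is standard, and 98, 220 and 258 all follow from it. This also stands. A reader might infer that the calculation ignores the 20 teams. It does not: it names 10 clusters per arm and inflates for them, and lacks only the small-sample correction. The gap between 258 and 259 is one client and immaterial.

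Third, the number of teams is not fixed, and adding one per arm at the same team size would restore 0.80. That is true, but the stated figure is for 10 per arm.

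Finally, one might argue that the ICC is really higher, given three treatment settings. The article offers no other value, and settings are matched before randomisation. Values of 0.02 to 0.05 would be a reviewer's assumption, so this point does not rest on them.

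**Conclusion.** The point holds in a limited form. On the stated two-sample t-test basis, power is overstated by about 4 percentage points: roughly 0.76 instead of 0.80, or equivalently a detectable difference of about 0.42 instead of 0.40. The cause is a large-sample approximation applied to 20 randomised teams, not an arithmetic slip.

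The figure assumes SD 1, ICC 0.01, equal teams of 11 evaluable clients and no covariate adjustment; unequal team sizes would lower it somewhat. It says nothing against the planned baseline-adjusted model, which reaches 0.80 at ICC 0.01 once the correlation is about 0.30.

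**What to change.** Keep the recruitment target of 258 and amend the Sample size text in one of two ways:

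1. State that the unadjusted team-level t-test (18 degrees of freedom, SD 1, ICC 0.01, 220 evaluable) has about 0.76 power, with 0.80 power for a difference of about 0.42.
2. Base the stated power on the planned baseline-adjusted mixed model, with 18 degrees of freedom and an explicit SD and baseline-to-12-month correlation, each with its source. This replaces the unquantified closing remark about mixed models.

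The second is preferable if a defensible correlation is available, because it describes the analysis that will be run. Showing power over a range of ICCs is optional. The cost is text only: design, recruitment and analysis are unchanged, and under the first option the quoted power becomes slightly less favourable.

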### Statistical analysis

Baseline data will be presented comparing the two treatment groups. Both intention-to-treat and per-protocol analysis will be conducted. To test the hypothesis that the tailored eHealth intervention will result in improved metabolic syndrome severity in SMI clients compared to usual care, linear mixed models will be used. The obtained betas describe the reduction in metabolic syndrome (Mets) Z score in the intervention group relative to the control group. Mixed-model analyses take the dependence of the repeated measurements into account, while using the maximum amount of information that is present in the data [49]. The main analyses will consist of fully corrected models. These models will be corrected for baseline values of the respective outcome plus include the covariates gender, age, and any other possible confounding variables on which the treatment groups differed at baseline. Also, ANCOVA will be used with the change of the Mets Z score (baseline – 12 months) as the outcome variable. Explanatory variables are gender, Mets Z score at baseline, and study group (intervention vs. control). The eHealth intervention succeeds if the lower mark of the two-sided 95% confidence interval is larger than zero. To test for within-group differences from baseline to the end of the intervention period, a repeated-measures ANOVA will be applied. The type-1 error is set to 5% (two-sided). For secondary outcomes, linear and logistic mixed models (depending on the outcome) will also be used to test the differences between the two groups. Missing values after 12 months will be conservatively replaced by the baseline-observation-carried-forward method to avoid an overestimation of the effect through dropouts.

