### Randomisation

Randomisation will take place at the team level, to avoid contamination between the intervention and control groups. Before the inclusion of clients, participating teams will be randomly assigned to the GILL eHealth intervention or the control group providing care as usual. This procedure will be performed by a statistician blinded to the characteristics of the teams using a computer-generated list of numbers. To optimise comparability of the subgroups, treatment settings (FACT, assisted housing, long-stay wards) will be matched before randomisation. Blinding of clients and participating teams is not possible due to the nature of the intervention.

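### Teams are randomised and the sample size allows for it, but the ANCOVA's listed terms leave team out and the mixed-model text does not mention it

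*Protocol article*

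**What the plan says.** The Randomisation section of the protocol article makes the team the randomised unit: "Randomisation will take place at the team level, to avoid contamination between the intervention and control groups". The Sample size section plans for the resulting correlation: "Assuming an inclusion of 10 clusters (teams) within each arm, and assuming an ICC of 0.01 implies that 220 patients are required".

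The Statistical analysis section then describes the between-group analyses:

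- **Linear mixed models** for the primary hypothesis, with fully adjusted models called the main analyses. The dependence they are said to handle is that between a client's own measurements: "Mixed-model analyses take the dependence of the repeated measurements into account". The adjustment terms are the baseline value, gender, age and variables that differ between arms at baseline.
- **An ANCOVA** of the change from baseline to 12 months, introduced as an addition: "Explanatory variables are gender, Mets Z score at baseline, and study group (intervention vs. control".
- **Linear and logistic mixed models** for the secondary outcomes, with no further detail.

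The section sets a two-sided type I error of 5%. It declares success if the lower limit of a two-sided 95% confidence interval is above zero. The article mentions no random team effect, cluster-robust variance or team-level degrees of freedom.

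**The concern.** Clients of one team share staff, setting and local practice, so their outcomes may be correlated. Because whole teams are allocated, that correlation enters the variance of the treatment difference. A model that treats clients as independent then gives a standard error that is too small and an interval that is too narrow.

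The Sample size section accepts this and pays for it with extra clients. The ANCOVA, with one change score per client and a listed set of terms, has nowhere to put it. Followed as written, it would declare a difference by chance more often than the stated 5%. The design and the analysis also contradict each other within one article.

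**Working it through.** **Inputs.** From the Sample size section: a difference of 0.40 in the Z score, power 0.80, alpha 0.05, 98 clients per arm, 10 teams per arm, ICC 0.01, 220 clients after clustering, 15% dropout, 258 recruited. The SD is not stated. I take it as 1, because the outcome is a Z score and this reproduces the plan's figure.

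**1. Reproduce the plan's sample size.**

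- Per arm: 2 × ((1.96 + 0.8416) / 0.40)² = 98.1 (plan: 98).
- With 20 teams and ICC 0.01: 196 × 0.99 / (1 − 196 × 0.01 / 20) = 215.1. That is 10.8 per team, rounded up to 11, and 11 × 20 = 220 (plan: 220).
- Dropout: 220 / 0.85 = 258.8 (plan: 258).

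The figures agree apart from rounding, so the sample size does contain a design effect for teams.

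**2. Type I error if team is ignored.** With m analysed clients per team, the design effect is DE = 1 + (m − 1) × ICC. A nominal 5% test that ignores it has a true two-sided error of 2 × (1 − Φ(1.96 / √DE)).

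At the plan's values, m = 220 / 20 = 11 and ICC = 0.01:

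- DE = 1 + 10 × 0.01 = 1.10
- 1.96 / √1.10 = 1.869
- two-sided error = 0.0617, about 6.2%
- interval coverage = 1 − 0.0617 = 0.9383, about 93.8%
- false success in one direction = 0.0617 / 2 = 0.0308, about 3.1%, against a nominal 2.5%

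If all 258 are analysed (the plan fills missing 12-month values with baseline values), m = 12.9, DE = 1.119, the error is 6.4% and coverage is 93.6%.

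**3. Other ICCs (assumptions, not in the document), m = 11.**

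| ICC | DE | Two-sided error |
|---|---|---|
| 0.01 (plan) | 1.10 | 6.2% |
| 0.03 | 1.30 | 8.6% |
| 0.05 | 1.50 | 11.0% |

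Simulated two-sample t-tests on 10 teams of 11 per arm (20,000 runs per ICC) gave 6.2% at 0.01 and 10.8% at 0.05. A t-test of team means on 18 degrees of freedom stayed between 4.6% and 5.0% across ICCs from 0 to 0.10.

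**4. Effect of baseline adjustment.** The figures above apply if the stated ICC is that of the outcome actually tested. The ANCOVA also adjusts for baseline, which changes the residual ICC. Simulating it without team (20 teams of 11, 8,000 runs), with an assumed client-level correlation of 0.7 between baseline and 12 months, gave these two-sided errors:

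| Team effects at baseline and 12 months | ICC 0.01 | ICC 0.03 | ICC 0.05 |
|---|---|---|---|
| Fully persistent | 5.5% | 5.4% | 5.7% |
| Correlated 0.7 | 6.1% | 8.6% | 10.7% |
| Unrelated | 8.5% | 14.6% | 19.2% |

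Baseline adjustment can therefore nearly remove the inflation or enlarge it. The document does not say which row applies.

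**5. Cost of including team.** At ICC 0.01 the standard error grows by √1.10 = 1.049, about 5%. Power with 220 analysed is Φ(0.40 / (√(2/110) × √1.10) − 1.96) = Φ(0.868) = 0.807, still above the planned 0.80 on the normal approximation that the plan's own figures follow.

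**The case against.** A reader might infer that none of the between-group analyses accounts for teams, that the interval deciding success is therefore wrong, and that the error rate is well above 10%. The document does not support this, for four reasons.

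- **The mixed-model text is silent, not exclusive.** The sentence on repeated measurements gives a reason for choosing mixed models. It does not set out the random effects, and none is listed. A random team intercept is compatible with it, and an article may leave that detail to a full protocol or analysis plan.
- **The success rule is not tied to the ANCOVA.** It follows the ANCOVA in the text, but the mixed models are called the main analyses, and their coefficients are also described as a reduction relative to control. A lower limit above zero fits either model.
- **The rule works in one direction.** The relevant nominal rate is 2.5%, so two-sided rejection rates overstate the chance of false success.
- **Only the ICC of 0.01 comes from the document.** There the excess is modest, and larger figures need assumptions about the ICC and about how far team effects persist.

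The planned within-group repeated-measures ANOVA also lends no weight, since it compares no groups and carries no success rule.

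All four points stand, and they limit the claim. They do not remove it: the ANCOVA's terms are listed and team is not among them, and the only dependence named for the mixed models is not the one that the randomisation creates.

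**Conclusion.** The point holds in a limited form. The clustering built into the randomisation and the sample size is not carried into the analysis text. For the ANCOVA this is a misspecification as written; for the linear and logistic mixed models it is an omission.

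On the plan's own figures (ICC 0.01, 11 analysed clients per team) the effect is mild: about 1.2 percentage points of extra two-sided error, and about 0.6 points of extra false success if the one-directional rule were applied to a model without team. These sizes assume equal team sizes and that 0.01 is the ICC of the outcome tested. A larger ICC would make the error worse, and baseline adjustment could move it either way. Because the bias favours finding a difference and the correction is cheap, it should be made before the data are analysed.

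**What to change.** Amend the Statistical analysis section to state that:

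- every between-group model (the primary mixed model, the ANCOVA, and the secondary linear and logistic models) includes a random intercept for team, with clients nested in teams where measurements are repeated;
- the linear models use a small-sample degrees-of-freedom correction suited to about 20 teams;
- one named model supplies the confidence interval that decides success.

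This changes wording only. The recruitment target stays, because 220 and 258 already include the design effect. Intervals become slightly wider: about 5% at ICC 0.01, plus a little more from the smaller degrees of freedom. That second part takes a little off the 80.7% power shown above, which rests on a normal approximation.
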